| List of Appendices Appendix 1 Inclusion exclusion flow chart for the diabetic cohort (CH1)  Appendix 2 Inclusion exclusion flow chart for the hypertension cohort (CH2)  Appendix 3 List of diabetic medication  Appendix 4 List of Read code for Essential Hypertension  Appendix 5 List of Read code for liver damage  Appendix 6 List of Read code of Anaemia  Appendix 7 List of BNF chapters for the HIV treatment  Appendix 8 List of BNF chapters for the malignancy treatment  Appendix 9 List of UGT1A1 inhibitors (list obtained from WHODrug Standardised Drug Groupings)  Appendix 10 List of covariates |

**Amendment -February 12^th^ 2021
E. Objectives, Specific Aims and Rationale,**

Objective for post-hoc analysis:

- To investigate the diabetic disease progression in relation to bilirubin levels in type2 diabetic patients.

| **Objective for post-hoc analysis**  4) To investigate the diabetic disease progression in relation to bilirubin levels in type2 diabetic patients, in a real-world setting. | **Outcome measure**  - Time to first introduction of additional anti-diabetic medication.  - Time to start of the insulin therapy | **Hypothesis tested**  4) Naturally elevated serum bilirubin level of type2 diabetic patients is associated with slower diabetic disease progression when measured by additional anti-diabetic medication therapy. |
| --- | --- | --- |

Rational:

In the analyses based on the original protocol, we found that high circulating bilirubin is associated with reduced renal diseases risk. We have based this analysis on two patient populations at risk of renal function decline, diabetes and hypertension. We have expected a much higher risk reduction for the diabetic patient cohort as bilirubin is known to increase insulin sensitivity, so the slower loss of glycemic control and bilirubin’s direct protective effect (through anti-oxidative effect) will reduce the kidney function decline. However, we did not find differences in risk reduction for both cohorts on the primary endpoint (eGFR decline, HR 0.88 for diabetic cohort and HR 0.91 for hypertensive cohort), while there was a larger risk reduction on the hypertensive cohort on the secondary endpoint (albuminuria, HR 0.89 for diabetic cohort and 0.82 for hypertensive cohort). This unexpected finding has made us required to directly evaluate bilirubin’s association with the key differences between these two cohorts (one cohort having normal glycemic control while the other has worse glycemic control)

Thus we propose a posthoc analysis of the associations between loss of glycemic control and circulating bilirubin. To reliably quantify the patients’ loss of glycemic control, we have chosen a commonly used endpoint in the clinical trials, “introduction to additional anti-diabetic therapy”, as an endpoint.

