| Study Background Bilirubin is the most powerful endogenous lipophilic anti-oxidant and is eliminated through glucuronidation by uridine diphosphate glucuronosyltransferase 1 family, polypeptide A1 (UGT1A1). It has been hypothesized that naturally elevated level of bilirubin has a protective effect against renal outcomes. The mechanism of action is proposed to be anti-oxidative, with effects on inflammation, endothelial function, dyslipidaemia, and platelet hyperactivity (1,2). Recent investigations indicate strong associations between naturally elevated bilirubin concentrations and positive renal outcome in diabetic and or hypertensive patients (3,4,5,6).  Most of the currently available studies (3,5,6) were conducted in Asia. It is therefore unclear if the results would be similar in non-Asian populations. Wagner et al. (7) showed that the natural bilirubin level is usually higher in Asians than Europeans, hence it is plausible that the findings based on Asian population (in 3,5,6) may not extend to the European population. To best of our knowledge, Riphagen et al. conducted the only study outside of Asia, showing a positive effect of bilirubin on a composite endpoint consisting of serum creatinine doubling or end stage renal disease (4).  All of these studies consisted of approximately 5000 subjects or less and may not have been able to account for critical confounders such as hemoglobin or smoking status which we hope to capture through a real-world study.  Prior studies focused on two patient populations at risk of CKD, diabetics or hypertensive patients. However, because different studies used different endpoints and slightly different methodologies, it is difficult to make direct comparisons on the potential effect of bilirubin in the two populations. Thus, by creating two cohorts, diabetic cohort and the hypertensive cohort from the same database and applying the identical analysis method we may be able to make direct comparisons on the effect of bilirubin on CKD in these two populations. |
| Study Type Observational study, part descriptive and part analytical. |
| Study Design This will be a retrospective open cohort study.  The first cohort (CH1) will be the population with a diagnosis date of type 2 diabetes. The second cohort (CH2) will be the population with a diagnosis date of essential hypertension. |

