| Definition of the Study population This study will examine two patient cohorts who are at risk of CKD, diabetic and hypertensive patients. Eligible patients must have information recorded at least 12 months prior to the study index date and have up to standard (UTS). The study population will include patient records from January 2005 to January 2019.  **Inclusion criteria**  Cohort 1 (CH1) will include type 2 diabetes mellitus (T2D) patients along with any one of the following criteria (see Appendix 1 for the inclusion exclusion flow chart):   - Newly diagnosed T2D (MEDCODE 758 : Type 2 diabetes mellitus) - 2 prescriptions of diabetic medication (See Appendix 3 for the list of all drugs) - Hemoglobin A1c (HbA1c) value greater than 6.5   Cohort 2 (CH2) will include essential hypertension (EHT) patients along with the following criteria (see Appendix 2 for the inclusion exclusion flow chart):   - Newly diagnosed essential hypertension (see Appendix 4 for list of Read codes)   Time related variable including the index date and the follow-up is described in the following figure:  **Rolling index date**  (The date first diagnosed with DM2 or HT**)**  Pre-index period  1 years  Acute disease period  2 years  Follow up period  (Median follow up 5 years, minimum follow up 1 year)  **End of follow up**  (Either the date patient has transferred out from the practice  Or the last date of the record in the dataset)  **CH1**: no DM2 diagnosis nor related medication during this period **CH2**: no HT diagnosis nor DM2 diagnosis nor related medication during this period  Baseline is characterized based on the observation in these periods  January 2005  January 2019  **Exclusion criteria**  We will exclude the following patients based on the Read code during acute disease period (2 years after the rolling index date):   - Liver dysfunction including drug induced liver injury (diagnosis with Read code listed in Appendix 5 and/or Aspartate transaminase (AST) and alanine transaminase (ALT) levels outside of the normal range (AST: 8-48U/L, ALT: 7-55U/L) - Anemia (hemoglobin level below cutoff, female:120 male:130 g/L, or with the clinical annotation of primary or secondary anemia with the Read code listed in Appendix 6) - Human immunodeficiency virus (HIV) infection and or on HIV related medications (see Appendix 7). - All malignancies and or on medications related to the treatment for the malignancies (see Appendix 8). - Age < 40 (to exclude type 1 diabetic patients). - Any user of UGT1a1 inhibitors (see Appendix 9) during the acute disease period. - < 1 year of clinical records in the database before the index date - Pregnant women - Patients with clinical record of alcohol dependencies. - Any patients with less than two bilirubin measurements during the acute disease period.   **Objective-specific exclusion criteria**  For each endpoint, we impose the following additional exclusion criterion:   - For objectives 1a) and 1b) with the endpoint “First two consecutive measurements of eGFR that are 30 percent less than the last eGFR record during the acute disease period”, we will exclude patients without eGFR records during the acute disease period (2 years after the rolling index date). - For objectives 2a) and 2b) with the endpoint “First observation of albuminuria (UACR >30mg/g) during the follow up period.”, we will exclude patients with recorded UACR more than 30mg/g during the acute disease period. - For objectives 3a) and 3b) with the endpoint “First observation of proteinuria during the follow up period, we will exclude the patients with the recorded proteinuria (protein dipstick test result +, ++, or +++) during the acute disease period. |

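### The amendment's contrast between the diabetic and hypertensive cohorts has no interval or test, and the protocol plans no between-cohort analysis to support it

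*Protocol*

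**What the plan says.** The Study Background explains why two cohorts are drawn from one database: by "applying the identical analysis method we may be able to make direct comparisons on the effect of bilirubin on CKD in these two populations". The listed objectives (1a to 3b) each concern one cohort and include no comparison between them.

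The Data/Statistical Analysis section plans a weighted Cox model within each cohort. Its only interaction tests are between exposure group and a list of patient characteristics and drugs. Cohort is not on that list.

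The Rational of the February 2021 amendment gives four hazard ratios: "eGFR decline, HR 0.88 for diabetic cohort and HR 0.91 for hypertensive cohort" and "albuminuria, HR 0.89 for diabetic cohort and 0.82 for hypertensive cohort". On the first pair it says "we did not find differences in risk reduction for both cohorts on the primary endpoint". On the second it says "while there was a larger risk reduction on the hypertensive cohort on the secondary endpoint". It continues: "This unexpected finding has made us required to directly evaluate bilirubin’s association with the key differences between these two cohorts", and describes that key difference as "one cohort having normal glycemic control while the other has worse glycemic control".

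On eligibility, the timeline figure in Definition of the Study population requires for CH2 "no HT diagnosis nor DM2 diagnosis nor related medication during this period". The period is apparently the year before index. Diabetes is not among the exclusions for the two years after index, and follow-up ends at transfer out or last record. CH1 does not exclude hypertension.

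**The concern.** Two hazard ratios from separately fitted models do not show by themselves whether the effects differ. That needs the difference of the log hazard ratios with its own standard error. The amendment draws opposite conclusions from two pairs of point estimates and gives the reader no means to check either one. Failing to see a difference for eGFR is not evidence of similarity, and a lower point estimate for albuminuria is not evidence of a larger effect.

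The interpretation also assumes that the cohorts differ cleanly in glycaemic control. On the visible text, a patient diagnosed with hypertension and later with type 2 diabetes can enter both cohorts, and would count in CH2 as having normal glycaemic control.

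Finally, the exposure split is at a population median, and the protocol does not say whether that median is taken per cohort. If it is, the two hazard ratios contrast different bilirubin levels.

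What is at stake is the between-cohort statement. The protocol commits to journal publication, so the statement may reach print. The within-cohort hazard ratios are not affected.

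**Working it through.** **The plan's own figure.** Schoenfeld's formula with HR 0.8, two-sided 5% (sidedness is not stated), 80% power and a 1:1 split gives 4 × (1.960 + 0.842)² / (ln 0.8)² = 631 events, as stated. Dividing by the assumed rate, 631 / 0.047 = 13 426 person-years, close to the stated 13 500. This covers the bilirubin effect within one cohort. No figure is given for a difference between cohorts.

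**Inputs.** The hazard ratios come from the amendment and the analysis-set sizes from Feasibility counts. Event counts are not given, so 3% to 20% of patients with an event is assumed, the same percentage in both cohorts.

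**Ratios of hazard ratios (CH2/CH1).**
- eGFR: 0.91 / 0.88 = 1.034, log 0.0335.
- Albuminuria: 0.82 / 0.89 = 0.921, log −0.0819.

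**Standard error.** With a median split, the variance of each log HR is about 4/D, where D is the number of events. For independent cohorts, SE = √(4/D1 + 4/D2). Weighting would usually make it larger.

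**Albuminuria**, with the row labelled albuminuria (45 168 and 79 975):

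| Patients with event | D1 | D2 | SE | z | p | 95% CI of ratio |
|---|---|---|---|---|---|---|
| 3% | 1 355 | 2 399 | 0.068 | −1.21 | 0.23 | 0.81–1.05 |
| 5% | 2 258 | 3 999 | 0.053 | −1.56 | 0.12 | 0.83–1.02 |
| 7.5% | 3 388 | 5 998 | 0.043 | −1.91 | 0.057 | 0.85–1.00 |
| 10% | 4 517 | 7 998 | 0.037 | −2.20 | 0.028 | 0.86–0.99 |
| 20% | 9 034 | 15 995 | 0.026 | −3.11 | 0.002 | 0.88–0.97 |

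**Which row is albuminuria?** Feasibility counts attaches that row to objectives 3a/3b, whereas the objectives table makes albuminuria 2a/2b. With the other row (66 317 and 84 335), p is 0.17, 0.078, 0.031, 0.013 and 0.0004. The 5% level is crossed at about 7.9% of patients with events under the first row and 6.2% under the second. The conclusion is the same either way.

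**eGFR** (66 509 and 81 025): p runs from 0.58 at 3% (CI of ratio 0.92–1.16) to 0.15 at 20% (0.99–1.08).

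**Shared patients.** Overlap breaks the independence assumption. With 3 000 albuminuria events per cohort, a correlation of 0, 0.1 or 0.3 between the two log hazard ratios gives p = 0.11, 0.09 or 0.06.

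**The case against.** The strongest reply is that comparing the cohorts is not an objective. It is a hope in the Study Background, worded with a may, so the absence of a planned test is no breach, and such detail can sit in a statistical analysis plan that is not shown. The amendment is a short rationale and not a results report, so a test may have been done and left out. Its main argument is that the authors expected a much greater risk reduction in diabetic patients and did not see one. Neither pair of estimates shows that, whether or not 0.82 against 0.89 is chance. The analysis is openly labelled post hoc.

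Most of this stands, and it limits the point. What remains is that the amendment states a difference and a non-difference as findings and shows nothing to support them.

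A reader might infer several stronger things that the documents do not support:
- **That the albuminuria contrast is false.** At the planning rate, 0.047 × 300 000 = 14 100 events per cohort would give p = 0.0006. That rate belongs to the eGFR endpoint, but a real difference cannot be ruled out.
- **That overlap produced the contrast.** Diabetic patients in CH2 would make the cohorts more alike, and positive correlation makes the independent-cohort standard error too large. Both work against a spurious difference.
- **That CH2 is screened for diabetes only in the year before index.** The figure has lost its layout and the Appendix 2 flow chart is not shown. The visible restriction also bars related medication, which narrows the gap.
- **That the bilirubin scales differ.** This holds only if the median is taken per cohort. Alternative cut-offs and continuous bilirubin are already planned within each cohort.
- **That Objective 4 is invalid.** It is a sound question within CH1 and does not depend on the contrast.

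**Conclusion.** The point holds as an unsupported statement, not as a demonstrated error. On the visible text, neither the larger effect in CH2 for albuminuria (ratio 0.921) nor the lack of difference for eGFR (ratio 1.034) can be judged. For albuminuria, p runs from about 0.2 to 0.002 over the assumed 3% to 20% of patients with events. This rests on independent cohorts, a 1:1 split, equal event percentages and no inflation from weighting. The eGFR result is compatible with no difference, but similarity is not shown.

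Normal glycaemic control in CH2 is not guaranteed after index by any text shown, and the extent of overlap is unknown. Objective 4 can inform the proposed mechanism within CH1. Because it runs in CH1 only, it should not be presented as explaining a difference between CH1 and CH2.

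**What to change.** 1. Add a stacked model of both cohorts with a cohort-by-bilirubin interaction on one common bilirubin scale (the same absolute cut-off, or per unit) and variance clustered on patient. Report the ratio of hazard ratios with its 95% CI for each endpoint.
2. Report how many patients are in both cohorts.
3. Add a sensitivity analysis that drops CH2 patients with evidence of type 2 diabetes (diagnosis code, anti-diabetic drug, or HbA1c above the CH1 threshold) up to the end of the acute disease period. Keep the CH2 definition itself unchanged, since redefining it now would be informed by the results.
4. Word the amendment's two between-cohort statements according to the interaction result, or call the comparison descriptive. Present Objective 4 as a question within CH1.

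The cost is one extra model and one sensitivity analysis on data already held, plus a wording change. The contrast may prove inconclusive, and the amendment would then have to say so.

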## Exposures, Outcomes and Covariates

**Outcome:**

Outcomes will include the following events:

Additional objective: diabetic disease progression

1) Time to first introduction of additional anti-diabetic medication.

- All anti-diabetic medication as listed in Appendix 3

- Insulin
